For all these reasons, the objectives of this MIVAS III study are to analyze the relationship between lifestyles (eating patterns, regular physical activity, smoking, and drinking) and the gut and oral microbiota, along with anthropometric parameters and aging arterial, cardiovascular, and neurocognitive health in the general Spanish population. Similarly, the mediating role of the gut and oral microbiota in the relationship between lifestyles and vascular health will be analyzed. Gender differences in the association of lifestyles with the composition of the gut and oral microbiota and vascular structure and function will also be analyzed. In addition, the study will examine the opinions and experiences of the population through a discussion group to facilitate the transfer from the study to routine clinical practice.

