### 2.2. Study population

One thousand participants will be selected from users of Spanish primary healthcare centers who meet the following inclusion criteria: being aged between 45 and 74 years and not meeting any of the exclusion criteria, which include the following: cardiovascular disease; body mass index (BMI) > 40 kg/m^2^; severe renal failure; chronic inflammatory or bowel disease; oncology disease under treatment; terminal state; pregnancy; and use of antibiotics in the previous 2 weeks. Participants will be recruited at health centers with the active participation of family doctors and nurses.

The sample size for this study was calculated with the free software GRANMO (http://www.imim.cat/ofertadeserveis/software-public/granmo/). The size necessary to detect the difference of 0.1 points in the alpha diversity of the microbiota (Shannon index) between the subjects that do or do not meet the Mediterranean diet criteria has been estimated. The proportion of compliance with the Mediterranean diet in the Evident II study was 30% (29). Therefore, assuming an alpha risk of 0.05 and a beta risk of 0.2 in a two-sided test, a common standard deviation of 0.4 (30), and a 5% dropout rate due to technical difficulties or refusal to participate, 190 subjects in the first group and 436 in the second are required to detect a difference ≥0.1 point between them in the Shannon index. On the other hand, assuming a rate of exposure of 0.3% (dysbiosis), in the control group, 471 subjects with vascular aging and 471 controls are required to detect a minimum odds ratio of 1.5 in the study factor (alpha diversity). Therefore, the 1,000 participants to be included in the study will be enough to test the mentioned hypotheses and will have an equal gender distribution.

While patients did not participate in the design of the study, they will actively participate in recruitment by disseminating the study objectives and inclusion criteria through their organizations. At the end of the study, in addition to sending a detailed report with the results of each patient, a dissemination session will be organized for all patients included in the study. Through discussion groups, the opinions and experiences of the population regarding the influence of microbiota composition on health will be investigated. Similarly, their attitudes and possible resistance will be considered for the transfer to clinical practice.

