
To examine whether the association between lifestyle and arterial aging is mediated by the intestinal microbiota, linear regression models will be fitted using bootstrapped mediation procedures included in the PROCESS SPSS macro (64). All variables will be analyzed disaggregated by sex, and differences with a gender perspective will be analyzed where appropriate since the influence of gender in many pathologies is known, particularly in cardio and cerebrovascular diseases.

The analyses will be conducted using the R v.4.2.1 program (65). R: A language and environment for statistical computing. R Foundation for Statistical Computing, Vienna, Austria (https://www.R-project.org/) and the statistical package SPSS for Windows version 28.0. (IBM, Armonk, New York: IBM Corp). A value of *p* < 0.05 will be considered statistically significant. Statisticians/researchers who perform different analyses will be blinded to patients' clinical data.

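### Sex differences in the lifestyle associations are an objective, but the only concrete method is sex-disaggregated analysis; a lifestyle × sex interaction should be named, with its limited power stated

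*Protocol article*

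**What the plan says.** The last paragraph of the Introduction (section 1) adds to the objectives "Gender differences in the association of lifestyles with the composition of the gut and oral microbiota" and with vascular structure and function. This asks about effect modification: is the lifestyle association different in women and men?

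Section 2.4 deals with sex in one sentence: "All variables will be analyzed disaggregated by sex, and differences with a gender perspective will be analyzed where appropriate". The first half fixes a procedure for every variable. The second half foresees some analysis of differences but gives no model, test, estimand or rule for when it applies. Section 2.4 names many methods, including ANCOVA, LASSO, ANCOM-BC, LEfSe, edgeR, hurdle and zero-inflated models, sPLS and a mediation macro. None is described as comparing an association between the sexes. The macro is cited for mediation only.

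Section 2.2 sizes the study on whole-sample comparisons. For the Shannon comparison it plans to "detect the difference of 0.1 points in the alpha diversity of the microbiota (Shannon index") between Mediterranean-diet adherers and non-adherers and concludes that "190 subjects in the first group and 436 in the second are required". It plans 1,000 participants with equal numbers of each sex, and gives no calculation per sex or for a difference between sexes.

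**The concern.** Two separate analyses answer two separate questions: is there an association in women, and is there one in men? Neither says whether the associations differ. When each half has only moderate power, one result will often cross the significance line and the other will not, even if the underlying associations are identical. A reader, or the study team, can then mistake that pattern for a sex-specific effect.

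What is at stake is the credibility of sex-specific statements in the results. The question arises for each pairing of a lifestyle factor (diet, activity, tobacco, alcohol) with a gut, oral or vascular outcome, so there are many openings for a chance contrast. Leaving the analysis of differences to be done where appropriate also allows the stratified results themselves to decide which contrasts are pursued.

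**Working it through.** **Inputs, all from section 2.2.** Difference 0.1 Shannon points; "a common standard deviation of 0.4"; 30% adherent; "assuming an alpha risk of 0.05 and a beta risk of 0.2 in a two-sided test"; "a 5% dropout rate due to technical difficulties or refusal to participate"; 1,000 participants, half of each sex. The article gives the 30% for the whole sample only. I assume that it and the SD apply equally in both sexes.

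**1. The plan's own figure.** Smaller group: n = (1 + 1/r) × [SD × (1.960 + 0.842)/difference]², where r is the ratio of the larger to the smaller group.
- With r = 2.3: n = 180.2 and 414.4. Dividing by 0.95 gives 189.7 and 436.2, which matches the stated 190 and 436.
- With the exact ratio 7/3: 188.8 and 440.6 after dropout, within about 1% of the stated figures.

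The inputs are therefore read as the plan used them.

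**2. Whole-sample power (300 vs 700).** SE = 0.4 × √(1/300 + 1/700) = 0.0276. Power = Φ(0.1/0.0276 − 1.96) = 95%.

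**3. Power within one sex (150 vs 350).** SE = 0.4 × √(1/150 + 1/350) = 0.0390. Power = Φ(2.56 − 1.96) = 72.6%. After 5% loss (142.5 vs 332.5), SE = 0.0401 and power is 70.4%.

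**4. Chance that exactly one sex is significant when the true effect is the same in both.** With per-sex power p this is 2p(1 − p).
- 500 per sex: 2 × 0.726 × 0.274 = 39.8% (both significant 52.8%, neither 7.5%). A simulation of 20,000 studies gave 39.6%.
- 475 per sex: 2 × 0.704 × 0.296 = 41.6%.

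**5. Dependence on the common true effect (500 per sex, unadjusted 0.05).**

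| Common true difference | Power per sex | Exactly one sex significant |
|---|---|---|
| 0 | 5.0% | 9.5% |
| 0.025 | 9.8% | 17.7% |
| 0.05 | 24.9% | 37.4% |
| 0.075 | 48.5% | 50.0% |
| 0.10 | 72.6% | 39.8% |
| 0.125 | 89.3% | 19.1% |
| 0.15 | 97.0% | 5.8% |

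A stricter threshold need not lower the figure. At a per-test level of 0.01 and a common effect of 0.1, power per sex is Φ(2.56 − 2.58), about 49%, and exactly one sex is significant about 50% of the time.

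**6. Direct test of the difference.** The SE of the between-sex difference is 0.0390 × √2 = 0.0552.
- False-positive rate when the effects are equal: 5% by construction (4.9% in the same simulation).
- Power for a true between-sex difference of 0.1: Φ(0.1/0.0552 − 1.96) = Φ(−0.149) = 44%; 42% with 950 evaluable.
- Difference detectable with 80% power: 0.0552 × (1.960 + 0.842) = 0.155; 0.159 with 950 evaluable.

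**The case against.** **The article does not state a wrong rule.** A reader might infer that sex differences will be claimed wherever one sex is significant and the other is not. The article never says so, and the second half of the quoted sentence does foresee an analysis of differences. This stands: the 40% describes a way of reading the stratified results that the plan leaves open, not one that it prescribes.

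**The model may be in an SAP that is not shown.** This is possible, and the absence of model detail alone would be no finding. But section 2.4 fixes stratification for all variables as the one concrete approach to sex, and stratification by itself does not answer the question posed in the Introduction. A better and nearly free method can be named, so the point survives as an improvement.

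**The 40% is one case.** It applies to one exposure, one outcome, one common effect size and an unadjusted 0.05. It cannot be carried over as a rate per association to smoking, alcohol, activity or single taxa, for which the article gives no effect size or SD. Section 2.4 also applies FDR adjustment to several comparisons. All of this stands, and the figure must be given with its conditions.

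**About 500 per sex does not contradict the sample size.** It is tempting to set 500 against 190 + 436 = 626 and call each half too small by the plan's own standard. Section 2.2 makes no power claim per sex, so no stated figure is broken. Sex differences are also absent from the main objectives in the Abstract and from the main and second objectives in the Discussion. They are an additional objective, in a study that describes itself as hypothesis-generating.

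**Conclusion.** The point holds in a limited form. A between-sex comparison of associations is an objective, the only concrete procedure stated is analysis by sex, and no between-sex test is named. If the sexes were compared by significance, a common true Shannon difference of 0.1 would appear in one sex only in about 40% of studies (39.8% with 1,000 participants, 41.6% with 950 evaluable), against 5% false positives for an interaction test. This rests on SD 0.4, 30% adherent in each sex, equal numbers of each sex and an unadjusted two-sided 0.05. Across common effects from 0 to 0.15 the figure runs from about 6% to 50%.

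The documents do not support saying that the study will produce spurious sex effects 40% of the time, or that its sample size fails its own requirement. The sized whole-sample comparisons are not affected. This is a cheap improvement to an additional objective and does not undermine the main analyses.

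**What to change.** For outcomes analysed by regression or ANCOVA, state that sex differences are estimated from the pooled model with a lifestyle × sex interaction. Report the difference in effect with its 95% confidence interval, and include the interaction p-values in the FDR family. Keep the sex-specific estimates with their intervals as descriptive results, and state that no difference will be inferred from significance in one sex only.

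LEfSe, Wilcoxon and chi-square comparisons, correlations and sPLS take no such term easily. Results by sex from these can stay descriptive.

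State the limit as well: about 44% power for a between-sex difference of 0.1 Shannon points (about 42% with 950 evaluable, less after FDR), with about 0.155 detectable at 80% power. A non-significant interaction is therefore not evidence that the associations are equal.

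The cost is one model term and a few sentences in the analysis plan, with no new data. The drawbacks are that fewer sex-specific claims will be possible and that the test would more likely than not miss a sex difference as large as the planned effect. If an SAP already specifies this, only the wording on interpretation and power needs checking.

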## 3. Discussion

This study aims to analyze the influence of different lifestyles on the composition of the gut and oral microbiomes. In addition, the influence of the microbiome on arterial aging and its impact on cardiovascular target organs, including the brain, will be evaluated by assessing neurocognition. Finally, the mediating role of the gut and oral microbiomes in the relationship between lifestyles, cardiovascular risk factors, and atherosclerotic disease will also be analyzed.

The human microbiota plays an essential role in health and the regulation of multiple physiological mechanisms (1). The concept of normal microbiota is still controversial since variability is important depending on multiple environmental and nutritional factors (30). In some studies, lifestyles have been shown to have a certain influence on the modification of the gut microbiota (66). Similarly, gut microbiota composition has also been implicated in the genesis of different diseases such as atherosclerosis (27), hypertension (67), obesity (68), insulin resistance, metabolic syndrome, and type 2 diabetes (69). In addition to the direct effects of diet on cardiovascular health, it is possible that it may exert effects through the gut microbiota, as has been observed in some cross-sectional and clinical trial studies (66), although the data are not conclusive. For example, a study with 893 participants estimated that the intestinal microbiota explained only 6% of the variance of triglycerides and 4% of HDL, regardless of age, sex, and genetic risk factors (70). On the other hand, good adherence to the Mediterranean diet has generally been associated with a beneficial gut microbiota composition (71).

The relationship between dietary patterns and the gut microbiome has been found in different studies, such as that of Latorre-Pérez et al. (30) in the general population, which confirms the association between some of the foods that characterize the Mediterranean diet and the abundance of bacterial taxa, and that of Wang et al. (72) in a diabetic population. Exercise has been linked to increased gut microbiota diversity in human cross-sectional studies (73). The beneficial effects of physical activity may be mediated, at least in part, by changes in the intestinal microbiota and its metabolites (74). However, in a study examining older men, the exercise program did not change composition compared to the baseline (75). Therefore, the relationship between exercise and microbiota is complex and insufficiently clear. Some studies have investigated the association of smoking with the gut microbiota, but they only showed a modest effect, and significant associations were not detected. Smoking may have indirect effects through alterations in the oral microbiota, and it is an important risk factor for periodontitis that is repeatedly associated with atherosclerotic vascular events (66). Low-grade inflammation has been proposed to be the cornerstone of different chronic diseases, such as metabolic syndrome (76), osteoarthritis (77), and type-2 diabetes (78). This inflammation has frequently been linked to an increase in intestinal permeability and a high intestinal translocation of proinflammatory mediators of bacterial origin, causing so-called “metabolic endotoxemia” and, therefore, the development of low-grade chronic inflammation and cardiovascular disease (79).

The MIVAS I (80) was a case-control study conducted in Spain (Salamanca) and Portugal (Guimaraes), with subjects from the EVA study (81) and the Cunha et al. (82), respectively, with the aim of analyzing the influences of gut microbiota on arterial stiffness. In this study, subjects with arterial stiffness and controls with the same characteristics were selected from the aforementioned studies. The MIVAS III study will select the general population of patients attended by family doctors and nurses in primary healthcare centers in different Spanish cities (Salamanca, Valladolid, Zaragoza, and Palma de Mallorca). The design is a multicenter cross-sectional study, with the main objective of analyzing the relationship between lifestyles (eating patterns, regular physical activity, smoking, and drinking) and the oral and gut microbiota. Second, the mediating role that the oral and gut microbiota may have in the relationship between lifestyle and arterial aging. In addition, the study will examine the opinions and experiences of the population through a discussion group to facilitate the transfer from the study to routine clinical practice. Finally, the second phase of the MIVAS III study will follow up on the cohort to analyze the effect of different oral and gut microbiota patterns on population health.

In conclusion, as previously discussed, healthy lifestyles, such as adequate dietary intake, a moderate or high level of physical activity, and not smoking, are beneficial for improving health and reducing the risk of many diseases, including cardiovascular diseases. It has also been found that lifestyles, particularly diet but also physical activity, act as modifiers of the composition and function of the microbiota. Nevertheless, no conclusive results have demonstrated the mediating effect of the microbiota in the relationship between lifestyles and cardiovascular diseases. Knowledge of the influence of different lifestyles on the composition of the gut and oral microbiome and of this on arterial aging and cardio- and cerebrovascular target organ lesions may facilitate the implementation of strategies to improve the health of the population by modifying the gut and oral microbiota.

The main limitations of the study are as follows: First, since it is not a random sample from the Iberian Peninsula, populational representation cannot be affirmed, although the fact that samples are collected in different locations across Spain could lend it a certain representativeness. Causality cannot be derived given the cross-sectional nature of the study, but it is possible to analyze the associations and generate hypotheses for future prospective etiological studies with cohort study designs and clinical trials. Nevertheless, the project has several strengths. With a sample of 1,000 participants from different parts of the Iberian Peninsula, it is larger than most of the published studies. Lifestyles and vascular health will be comprehensively assessed, in addition to the gut and oral microbiota. The participating clinical and basic researchers are from different areas of the Iberian Peninsula, which will facilitate the transfer of research results to the Spanish and Portuguese health systems as the first step in the internationalization of the project.

## 4. Summary

Evidence of the importance of microbiota in relation to multiple health processes is growing. Knowledge of which lifestyles can influence it can aid in the development of strategies to promote changes in diet, physical activity, and other habits that allow the microbiota to be modified to healthy profiles. This observational project is the first phase of future clinical trials that evaluate interventions on lifestyles to achieve healthy microbiota and, with it, reduce the risk of certain pathologies. It also addresses the relevant problem of how the different microbiome patterns are associated with vascular structure and function (arterial aging), damage to cardiovascular target organs, and cognitive impairment. Identifying microbiome patterns related to aging and highly prevalent processes will facilitate interventions to preventively modify them. Similarly, the mediating role of the microbiota in the relationship between lifestyle and arterial aging will be analyzed. Finally, the intention is also to contribute to the development of a methodology so that microbiota analysis can be transferred to clinical practice and contribute to the development of personalized medicine.

## Ethics statement

The studies involving human participants were reviewed and approved by the Committee of ethics of research with medicines of the health area of Salamanca on 13 November 2020 (cod. 2020 10 568). The patients/participants will be required to provide their written informed consent to participate in this study.
